#### Secondary outcome measures

2.8.2

The difference between groups in the change in individual urine output (with 95% CIs) at 2 hoursDuration of consecutive oliguria (urine output <0.5 mL/kg)
Hours from randomization, assessed until resolved for the first time/patients is discharged/RRT is commenced)Cumulative fluid balance on study day
6 hours from randomization

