### Exploratory outcomes

2.9

Physiological effects from randomization until measured at 2 hours
Mean arterial pressureHeart rateNorepinephrine doseCentral venous pressure (among those with central line)Difference in core vs peripheral temperatureCapillary refill time (until 60 minutes)Blood pHStandard base excessArterial lactateNumber of patients receiving rescue boluses and the number of rescue boluses
From randomization to 2 hours post‐randomizationNumber of patients with one or several protocol violation(s) and the number of those per patient
From randomization to 2 hours post‐randomization

Protocol violations include the following:
Patient received Furosemide or other diuretic during the 2‐hour periodChanging MAP target (defined as MAP level increased from baseline target AND increased vasopressor dose from the baseline)No full 500 mL bolus in bolus groupFluid bolus (other than rescue bolus) in the follow‐up groupErroneously randomized non‐eligible patient
d.Number of patients with adverse events
Assessed from randomization until the next morningDefined as events reported by the treating clinician in the open questionnaire included in the protocole.Highest AKI stage within
(i)24 hours(ii)48 hours(iii)During ICU stayf.Number of patients receiving renal replacement therapy (during ICU stay)

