#### Secondary and exploratory outcomes

2.11.3

As the primary outcome, the secondary and exploratory outcomes will be adjusted for the two stratification variables.^25^ Continuous measures will be expressed according to their distribution and difference between the groups in the change in individual urine output, duration of consecutive oliguria, and cumulative fluid balance on study day will be compared using mean or median regression depending on normal distribution and expressed with 95% CIs. Dichotomous endpoint measures (number of patients receiving rescue boluses, highest AKI stage within 24, 48 hours and during ICU stay, and number of patients receiving RRT) will be analyzed using ordinal or logistic regression and reported as risk ratios with 95% CIs. Furthermore, crude event rates and risk rations will be reported for dichotomous outcomes and absolute differences with 95% CIs for continuous outcomes.

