#### Missing data

2.11.5

We do not expect to have missing data about the primary outcome measure or stratification variables in the ITT population. Regarding secondary or exploratory outcomes, some missingness is expected (for example CVP values in patients who have not a central line inserted), but imputation will not be used. Regarding other data points, if the amount of missing observations regarding other variables is less than 5%, we do not impute data. Regarding descriptive data, an appropriate multiple imputation strategy according to the type of missingness (missing at random or missing completely at random) will be used if missingness exceeds 5% of observations.

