### Sample size

2.12

No reliable previous data to inform about the incidence of the primary outcome were available. Among oliguric (urine output <0.5 mL/kg/h for at least 3 hours), hemodynamically stable patients, 50% were considered as renal responders to a fluid challenge that constituted at least one 500 mL crystalloid bolus administered over 15 minutes.^10^ In that study the definition of a positive renal response (post‐bolus urine output over 0.5 mL/kg/h for at least 3 hours) was more liberal than in our trial.^10^ Fluid bolus did not significantly increase urine output among patients with acute respiratory distress syndrome (both oliguric and non‐oliguric).^5^ Therefore, we assume that 30% of patients in the fluid bolus group will be endpoint‐positive. Additionally, we consider 20% absolute difference (which translates to a number needed to treat of 5) as a minimum clinically meaningful difference between the groups to support the use of such a common and inexpensive intervention. Thus, to reach a 20% absolute difference in the primary outcome (30% in the fluid bolus group and 10% in the noninterventional follow‐up group), 62 patients per group will be required to reach 80% power with significance level set at .05 (two‐sided). Considering possible drop‐outs we aim to randomize 65 patients per group to target at least 62 patients per group in the ITT population.

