## DISCUSSION

3

Albeit fluid bolus therapy is frequently used in oliguria to increase urine output, the success of this intervention is largely unknown. The RESPONSE trial will give high‐quality information about the physiological outcomes of fluid bolus therapy given for oliguria in hemodynamically stable patients compared to a follow‐up treatment strategy without additional fluids. Conservative fluid resuscitation strategies especially in septic patients are actively investigated^28^, ^29^ as the evidence regarding harms of fluid overload are being increasingly recognized, especially among patients with AKI.^30^, ^31^ The results of RESPONSE trial will help to assess the potential benefit of fluid bolus therapy, and if no clinically meaningful improvement on urine output or other physiological variables can be demonstrated, will help in avoiding unnecessary fluid loading in the future.

The randomized approach in studying the response of fluid bolus therapy to an alternative intervention is an obvious strength of our study, as the current evidence is based on observational data. Moreover, we are carefully recording data on other fluid input and output, common hemodynamic parameters, acid‐base balance, and blood gases. Thus, we will be able to provide a detailed analysis on the effects of fluid bolus on these parameters as compared to the follow‐up approach. Additionally, we will include a heterogeneous population of critically ill patients with oliguria who have received the initial fluid resuscitation, which will improve the generalizability of our results.

Our trial has some obvious limitations. First, the intervention is not blinded from the clinical team or the investigators due to its nature. Potentially, clinician aware of the patient being in the follow‐up group may give a fluid bolus after the intervention period, and therefore neutralizing the difference between the groups regarding fluid balance. However, we record the details of urine output and fluid therapy until 6 hours post‐randomization to assess the administration additional fluid boluses. Moreover, the trial statistician will be blinded to the group allocation. Second, our trial protocol does not mandate cardiac output monitoring, and therefore, commenting whether patients were hemodynamic fluid responders will not be possible. However, numerous studies have shown that global hemodynamics and renal hemodynamics do not correlate.^7^, ^10^

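### Duration of oliguria stops at RRT or discharge but is analysed as a completed duration, so an arm with more early RRT looks better on this secondary outcome

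*Protocol article*

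**What the plan says.** Under Secondary outcome measures (2.8.2), the protocol article lists duration of consecutive oliguria and defines its end: "Hours from randomization, assessed until resolved for the first time/patients is discharged/RRT is commenced". Three different events can thus close the count. Death is not among them, and the text does not say whether discharge means from the ICU or from hospital.

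Under Secondary and exploratory outcomes (2.11.3) the model is fixed: "duration of consecutive oliguria, and cumulative fluid balance on study day will be compared using mean or median regression depending on normal distribution". The same section says that "the secondary and exploratory outcomes will be adjusted for the two stratification variables", namely AKI and sepsis.

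Two other places could have repaired this and do not. Missing data (2.11.5) says of secondary and exploratory outcomes only that "some missingness is expected (for example CVP values in patients who have not a central line inserted), but imputation will not be used". Exploratory outcomes (2.9) counts patients who receive RRT during the ICU stay, but as a separate outcome with no link to the duration.

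**The concern.** The three end reasons differ in meaning. Resolution is the event of interest and is favourable. RRT is unfavourable and ends any observation of native recovery. Discharge with ongoing oliguria says only that the duration was at least that long. The planned regression takes a number of hours and has no place for the reason, so RRT at 3 h counts the same as recovery at 3 h. Choosing between mean and median regression by a normality check deals with skewness. It does not deal with censoring or competing events.

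The trial asks whether withholding a bolus is acceptable. A renal secondary outcome on which treatment failure shortens the score could favour whichever arm has more failures. Both the stopping rule and the model are stated in the article, so this is a rule fixed badly and not a detail left to an unseen document.

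**Working it through.** **Plan's own figure.** None is given for this outcome. The only sample-size figure is for the primary outcome: "62 patients per group will be required to reach 80% power". For 30% versus 10%, two-sided 0.05, pooled variance and no continuity correction:

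n = [1.960·√(2·0.2·0.8) + 0.842·√(0.3·0.7 + 0.1·0.9)]² / 0.2² = (1.109 + 0.461)² / 0.04 ≈ 61.6, so 62.

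It reproduces (power 80.3%) and is used below only as the arm size.

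**Inputs for the illustration (all assumed).** The article gives neither an RRT rate nor a distribution of durations. Assume time to resolution is exponential with rate λ = 0.1/h (mean 10 h) in both arms, and RRT occurs at constant rate μ, which differs by arm. Discharge and death are left out.

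**Formulae.**
- Share ended by RRT: p = μ/(λ + μ).
- Planned mean: 1/(λ + μ) = 10(1 − p).
- Planned median: ln 2/(λ + μ) = 6.93(1 − p).
- Cumulative incidence of resolution by 12 h, with RRT competing: (1 − p)·[1 − exp(−12(λ + μ))].
- Median with RRT ranked worst: the t that solves (1 − p)·[1 − exp(−(λ + μ)t)] = 0.5.

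| RRT before resolution, p | Planned mean (h) | Planned median (h) | Resolved by 12 h | Median, RRT worst (h) |
|---|---|---|---|---|
| 3% | 9.7 | 6.72 | 69% | 7.0 |
| 5% | 9.5 | 6.58 | 68% | 7.1 |
| 17% | 8.3 | 5.75 | 63% | 7.7 |

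**Between-arm differences under the plan as written.**
- 3% versus 5%: mean 9.7 − 9.5 = 0.2 h; median 6.93 × 0.02 = 0.14 h, about 8 minutes.
- 5% versus 17%: mean 9.5 − 8.3 = 1.2 h; median 6.93 × 0.12 = 0.83 h.
- Equal shares: no difference.

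In both unequal cases the arm with more RRT looks better on the planned measures and worse on the last two columns.

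**Against sampling error.** An exponential standard deviation equals its mean. At 5% versus 17% with 62 per arm, the standard error of the mean difference is √[(9.5² + 8.3²)/62] = √(159.1/62) ≈ 1.6 h. The 1.2 h bias is below one standard error.

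**Different assumptions, same direction.** Take a median time to resolution of 6 h in patients who do not go to RRT, and RRT started uniformly between 1 and 4 h in the rest (simulated, 400,000 draws). Going from 0% to 10% RRT moves the planned median from 6.0 to 5.1 h. With RRT ranked worst, the median moves from 6.0 to 7.0 h.

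**The case against.** **Size.** The larger scenario needs a wide imbalance from a single 500 mL bolus given or withheld: 5% versus 17% of 62 is about 3 versus 10 or 11 patients. The Exclusion criteria (2.6.2) remove patients with an urgent indication for RRT, existing RRT, chronic kidney disease or marked fluid overload. Only RRT before the first resolution distorts the measure, which is narrower than any RRT in the ICU. RRT is also reported separately, so a marked imbalance would be visible. All of this stands. It limits the likely size but does not make the scoring rule right.

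**Remedy.** Cumulative incidence and worst-rank scoring answer different questions. Censoring at discharge assumes that discharge is unrelated to recovery, which is doubtful. This stands as a caution about the fix.

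**Stronger readings that the article does not support.**
- A reader might infer that every duration is cut off at 6 h, because the Discussion says "we record the details of urine output and fluid therapy until 6 hours" after randomization. That sentence concerns detecting additional boluses after the intervention period. The outcome definition runs until first resolution, and the supplement listing the data items (Data S1) is not shown. No 6-hour censoring can be concluded.
- A reader might infer that death is a major gap because it is not a listed end. Patients expected to survive less than 24 hours are excluded, so death before first resolution should be uncommon. It needs a rule but is a minor part of the point.
- A reader might infer that the comparison will be seriously biased. Without an RRT rate, that cannot be claimed.

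**Conclusion.** The point holds. The stopping rule and the regression model together score RRT and discharge while oliguric as completed durations, and nothing else in the article corrects this. Where arms differ in early RRT, the error favours the arm with more of it. In the exponential illustration the distortion runs from about 0.1 h in the median (3% versus 5%) to about 0.8 h in the median and 1.2 h in the mean (5% versus 17%). It is zero in that model if the shares are equal, although the outcome then still mixes recovery with failure. These figures rest on assumed rates and an assumed distribution. The consequence is confined to one secondary outcome; the primary outcome and its sample size are untouched. The change is worth making because it is cheap and can be specified before the data are seen.

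**What to change.** Choose one of two forms and state it in 2.8.2 and 2.11.3.

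1. **Preferred.** Define the outcome as time from randomization to first resolution of oliguria. Treat RRT, and death before resolution if it occurs, as competing events. Censor at discharge while still oliguric, and say which discharge is meant. Present cumulative incidence of resolution by arm, with a model adjusted for AKI and sepsis, such as Fine-Gray.
2. **Alternative.** Keep duration in hours and give RRT and death before resolution the worst rank. The model must then be median regression, fixed in advance and not chosen by a normality test, because a mean cannot carry a worst rank. This form does not by itself resolve discharge while oliguric, which still needs a stated rule.

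Under either form, report by arm the number of patients whose assessment ended by resolution, RRT, discharge while oliguric, or death.

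**Cost.** Slightly more analysis work, and an assumption under form 1 that discharge is non-informative. Time of death is also needed for any patient who dies before resolution: Data collection (2.10) mentions only vital status at hospital discharge or day 30, so the sponsor should check whether the time is captured. The sample size does not change.

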### Exploratory outcomes

2.9

Physiological effects from randomization until measured at 2 hours
Mean arterial pressureHeart rateNorepinephrine doseCentral venous pressure (among those with central line)Difference in core vs peripheral temperatureCapillary refill time (until 60 minutes)Blood pHStandard base excessArterial lactateNumber of patients receiving rescue boluses and the number of rescue boluses
From randomization to 2 hours post‐randomizationNumber of patients with one or several protocol violation(s) and the number of those per patient
From randomization to 2 hours post‐randomization

Protocol violations include the following:
Patient received Furosemide or other diuretic during the 2‐hour periodChanging MAP target (defined as MAP level increased from baseline target AND increased vasopressor dose from the baseline)No full 500 mL bolus in bolus groupFluid bolus (other than rescue bolus) in the follow‐up groupErroneously randomized non‐eligible patient
d.Number of patients with adverse events
Assessed from randomization until the next morningDefined as events reported by the treating clinician in the open questionnaire included in the protocole.Highest AKI stage within
(i)24 hours(ii)48 hours(iii)During ICU stayf.Number of patients receiving renal replacement therapy (during ICU stay)

### Data collection

2.10

Trained research personnel will perform data collection using an electronic platform (Absolute Imaginary Software Ltd). Data S1 comprises the detailed list of collected data items. In brief, patient characteristics at baseline will be collected, and details of urine output, hemodynamics, and fluid therapy will be recorded during the intervention and follow‐up period. Patients’ vital status will be recorded at hospital discharge or on day 30 whichever comes first.

### Statistical analysis

2.11

#### General analytical principles

2.11.1

Statistical analyses will be performed on the intention‐to‐treat (ITT) population defined as all randomized subject excluding (a) those without consent (b) ineligible subjects who were erroneously randomized and did not receive the trial intervention. The conclusions of the analysis will be based on the ITT analysis.

A sensitivity analysis will be conducted in the per‐protocol population, defined as the ITT population and excluding subjects (a) who experienced one or several protocol violations or (b) who received the rescue bolus.

Continuous variables will be checked for normality using the Shapiro‐Wilk test. We will set statistical significance to .05 and report two‐sided *P*‐values.

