### Blinding

2.5

Due to the nature of the study, blinding of the ICU personnel is not feasible. The allocation is blinded for the statistician conducting the data analysis. Additionally, we will write an abstract of study results prior to becoming aware of the group allocation and will include this abstract in the appendix of the original publication. Use of randomization blocks of varying size not known for clinicians prevents knowledge of treatment allocation before randomization.

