#### Intervention group (noninterventional follow‐up)

2.7.1

Patients in the intervention group will not receive fluid bolus or diuretics to increase urine output during the 2‐hour intervention period.

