#### Standard group (fluid bolus group)

2.7.2

Patients will receive 500 mL intravenous crystalloid (Ringer's acetate) infused over 30 minutes using an infusion pump.

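### The ITT exclusion of ineligible patients who did not receive the intervention has no clear meaning in the follow-up arm, so it can operate differently by arm

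*Protocol article*

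**What the plan says.** All references are to the Protocol article.

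- **2.11.1 General analytical principles** defines ITT as all randomized subjects minus two groups: (a) those without consent and (b) "ineligible subjects who were erroneously randomized and did not receive the trial intervention". It adds: "The conclusions of the analysis will be based on the ITT analysis".
- **2.11.1** also defines the only stated sensitivity population, per-protocol, as the ITT population minus patients with a protocol violation or a rescue bolus. Section 2.9 lists randomization of a non-eligible patient as a protocol violation.
- **2.7.2 Standard group**: the bolus arm receives 500 mL of crystalloid, "infused over 30 minutes using an infusion pump".
- **2.7.1 Intervention group**: "Patients in the intervention group will not receive fluid bolus or diuretics to increase urine output" during the 2-hour period.
- **2.5 Blinding**: "blinding of the ICU personnel is not feasible". Only the statistician conducting the analysis is blinded.
- **2.12 Sample size**: 65 per group are randomized "to target at least 62 patients per group in the ITT population".

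**The concern.** Exclusion (b) has two conditions: the patient was ineligible, and the patient did not receive the trial intervention. The first can be settled from facts that precede randomization, although the text does not require this. The second is settled afterwards, by staff who know the allocation, and it means different things in the two arms.

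Staff about to start a 500 mL infusion have a reason to notice a problem such as pulmonary edema or fluid overload and to hold the infusion. That patient then leaves the ITT set. In the follow-up arm there is no infusion to hold, so no equivalent act marks a patient as untreated. Two patients with the same eligibility error could be handled differently because of their allocation.

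The protection that randomization gives to the main comparison is at stake. The trial hypothesizes no clinically significant difference (Introduction), and a finding of no meaningful improvement would be used to discourage fluid loading (Discussion). A bias toward no difference therefore matters as much as one away from it.

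**Working it through.** **1. The plan's own figure.** The inputs from 2.12 are 30% versus 10% and "80% power with significance level set at .05" (two-sided). With pooled variance, no continuity correction and a mean proportion of 0.20:

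n = [1.960 × √(2 × 0.20 × 0.80) + 0.842 × √(0.30 × 0.70 + 0.10 × 0.90)]² / 0.20² = (1.109 + 0.461)² / 0.04 ≈ 61.6, so 62 per group.

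The stated 62 is reproduced (power 80.3%). The allowance for all losses from ITT is 65 − 62 = 3 per group (4.6%).

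**2. What the second condition means in each arm.**

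| Arm | Allocated care | When the intervention was not received |
|---|---|---|
| Bolus | A discrete infusion | The infusion was not started: identifiable |
| Follow-up, reading A | Nothing is given | True of everyone: all ineligible patients are dropped |
| Follow-up, reading B | Allocation itself is the intervention | True of no one: all ineligible patients are kept |
| Follow-up, reading C | Two hours without bolus or diuretic | True only of those given a bolus or diuretic |

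The text does not choose between A, B and C. None of them matches the bolus-arm rule. Under C, exclusion depends on an active clinical decision, possibly prompted by the patient's course.

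**3. Whether the per-protocol analysis can check this.** It starts from the ITT set, so it never restores a dropped patient. It also removes the remaining ineligible patients together with all other protocol violators and rescue-bolus recipients. A gap between the two analyses could not be traced to exclusion (b).

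**4. Possible size.** The number of such patients, k, and their response rate, q, are not in the document and are assumed here. Take no true effect, 20% responders among eligible patients in both arms, 65 per arm, and k ineligible patients per arm who are dropped from the bolus arm only (reading B, every infusion withheld). The bolus arm shows 0.20 and the follow-up arm shows [(65 − k) × 0.20 + k × q] / 65. Bolus minus follow-up is therefore k × (0.20 − q) / 65.

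| k | q = 0 | q = 0.5 | q = 1 |
|---|---|---|---|
| 3 | 0.6/65 = +0.9 points | −0.9/65 = −1.4 | −2.4/65 = −3.7 |
| 5 | 1.0/65 = +1.5 points | −1.5/65 = −2.3 | −4.0/65 = −6.2 |

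If the patients are dropped from the follow-up arm only, the signs reverse. The shift is zero if k = 0 or q = 0.20.

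**5. The same under the planned effect.** Take 30% versus 10% among eligible patients, k = 3, and the same q in both arms because these patients are untreated. Dropping from the bolus arm only gives 0.30 − (6.2 + 3q)/65, which is 20.5 points (q = 0) to 15.8 points (q = 1). Dropping from the follow-up arm only gives (18.6 + 3q)/65 − 0.10, which is 18.6 to 23.2 points.

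**6. Yardstick.** At 20% responders and 62 per arm, the standard error of the difference is √(2 × 0.20 × 0.80 / 62) = 7.2 points.

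**The case against.** The strongest reply is that the follow-up arm is more than the absence of a bolus. It is a defined 2-hour regimen: no bolus or diuretic, ongoing infusions held constant, and advice against changing the MAP target (2.7.1, 2.7.3). A patient found ineligible and taken off that regimen could reasonably be said not to have received it, so the rule can operate in both arms. This stands against the claim, which a reader might infer, that the condition must be true of everyone or of no one in the follow-up arm. It does not remove the problem, because the article does not adopt this reading and it still gives the two arms different triggers.

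The reply on size also stands in part. Eligibility is rechecked when oliguria develops (2.6), so errors should be few. Exclusion (b) touches only those who are both ineligible and untreated. The illustrated shifts for three patients are well inside one standard error, and q = 1 is an extreme.

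Some handling exists elsewhere: erroneous randomizations are counted as violations (2.9) and participant flow follows CONSORT (2.14). That would make exclusions visible, but it would not make the rule the same in both arms.

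A separate SAP might define receipt of the intervention. The article, however, says it summarizes the protocol and a detailed analysis plan, and it states this rule itself. The Supplement is cited for eligibility definitions, not for analysis sets.

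**Conclusion.** The point holds as a defect in a stated rule: membership of the population that carries the conclusions depends on a post-randomization condition that is clear in one arm and undefined in the other. No blinded assessment of eligibility is stated.

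The likely effect is small and its direction cannot be known in advance. With three such patients per arm, equal to the whole allowance for losses, the shift under no true effect lies between +0.9 and −3.7 points. With five it lies between +1.5 and −6.2. Both ranges rest on the assumed k and q, and on exclusion from the bolus arm only.

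A reader might go further and infer that differential exclusion will occur, that the randomized comparison is broken, or that the sample size is wrong. The document supports none of these. It shows an ambiguity that permits differential exclusion, it gives no number of ineligible patients, and the 62 per group is reproduced.

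**What to change.** Delete the whole of exclusion (b) in 2.11.1 and define the main population as every randomized patient with consent, analysed in the assigned arm. This is a one-sentence change.

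If ineligible patients are still to be excluded, then:

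- base the exclusion only on facts that precede randomization;
- have it judged blind to arm and outcome;
- apply it identically in both arms, whatever treatment was received;
- report the exclusions by arm;
- add a sensitivity analysis in all randomized patients with consent.

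Do not merely strike the words about not receiving the intervention. On its own that would exclude all erroneously randomized patients and widen the exclusion.

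The cost is slight dilution. Under the planned 30% versus 10%, keeping 3 untreated ineligible patients in each arm, with equal response, gives 0.20 × 62/65 = 19.1 points instead of 20.0. Keeping 5 gives 0.20 × 60/65 = 18.5. The target sample size need not change: 65 per arm has 82.1% power for the 20-point difference before any dilution. The consent exclusion (a) remains, so the set would still not be strictly all randomized patients and should be described accordingly.
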